### Study setting

The study will be conducted in 16 French hospital centers with a network of primary care dermatologists in France.

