### Recruitment

Particular attention will be given to recruiting a primary care population. Each region is organized from a university-based dermatology department into several ‘field study sites’ gathering several participating primary care dermatologists.

Meetings will be organized with primary care dermatologists to invite them to participate and to inform them on how the study will unfold. A trained study nurse will help them check their patients’ eligibility and plan the visits. The patients will have the possibility of receiving their phototherapy with their primary care dermatologist; scheduled visits will take place every 6 weeks.

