### Assignment of interventions

#### Sequence generation and allocation concealment mechanism

Participants who meet the eligibility criteria and have signed informed consent will then be randomly assigned, in a 1:1 ratio, to either vitamin D or placebo, and within each arm to either the sequence UV–observation or the sequence observation–UV through an automated web-based system. A permuted block randomization scheme will be used, with stratification according to the clinical site, age (three age groups) and disease severity (two groups: moderate or severe). The list will be balanced by blocks of random size in order to ensure total unpredictability. Randomization can occur on the day of inclusion (Visit 1).

Since we offer phototherapy sessions exclusively during winter periods, the carry-over effect is not a concern in our study (Fig. 2).

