#### Statistical methods

The statistical issue for the primary outcomes is the analysis of repeat measures (up to 12 measures for each 1-year period, on the PO-SCORAD, a self-administered questionnaire the results of which are collected through an application on computer or phone, at home) applied to a crossover design (two 1-year periods, two sequences). When repeat measures are analyzed, there are many possible hypotheses that could be of interest. We focused on a main effect hypothesis test for the effect of a single predictor variable (treatment: phototherapy) averaged across all other factors, and the sample size calculation was designed accordingly. We are interested in the usual factors, namely ‘Treatment’ (phototherapy/no phototherapy) and ‘Time’. However, the nature of the design (crossover trial) needs to be taken into account. This means that we need to consider the following factors: ‘Period’ – first winter/second winter, ‘Order’ – phototherapy–no phototherapy or no phototherapy–phototherapy, and ‘Carry-over’. It was anticipated that vitamin D could act as a quantitative effect-modifier on phototherapy. We therefore decided to include an interaction term in the analysis. We will use a single model with the following main effects: Treatment-1 (phototherapy/no phototherapy), and Treatment-2 (vitamin D/placebo), Period, Order, and Carry-over terms as well as an interaction term between Treatment-2 and Treatment-1. As an interaction of Time and Treatment could occur, we plan to add an interaction term to the model. The other primary outcome, the cumulate consumption of TAT (number of tubes) during the winter, is a quantitative variable. It will be analyzed using a mixed model with the following main effects: Treatment-1 (phototherapy/no phototherapy), and Treatment-2 (vitamin D/placebo), Period, Order, and Carry-over terms as well as an interaction term between Treatment-2 and Treatment-1. As this outcome is a summary of winter consumption, no interaction of Time and Treatment will be added to this model. Adjustment will be made on the variables used in the allocation process (region – north vs. south), age as a continuous variable, and disease severity (moderate vs. severe).

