For descriptive purposes, it is instructive to carry out an analysis based on a summary of the statistics (a quantity calculated from each curve), which can reflect important aspects of the problem at hand – we have chosen the area under the curve (AUC) and the mean amplitude of PO-SCORAD score ranges. Descriptive statistics (mean and standard deviation) of the PO-SCORAD for each visit will also be provided. Normal distribution is assumed in the modeling analysis for the primary outcomes (PO-SCORAD severity score over two 1-year periods; cumulate consumption of TAT during winter) and will be checked at this stage.

The main analysis will be based on the adjusted model and will follow the ‘intention to treat’ principle, namely all participants, as randomized, will be analyzed; outcome data obtained from all participants, regardless of protocol adherence, will be used. Mixed model techniques (PROC MIXED) will be applied.

The multiplicity adjustment strategy used is a hierarchical closed test procedure, where the primary endpoints are ordered as follows: (E1) repeat measures of the PO-SCORAD severity score over 1 year and (E2) cumulate consumption of TAT over winter. We will test E1 and E2 sequentially at the same two-sided level of 0.05; we will test E1 first, if it proves significant, will we test E2. A Wald test with Kenward–Roger degrees of freedom will be used.

No subgroup analyses nor interim analyses are planned.

For secondary analyses, we will use up to four measures per 1-year period, collected at each clinical visit (every 3 months), including investigator-based severity scores (Eczema Area and Severity Index, Severity of Atopic Dermatitis Index, Investigator Global Assessment), patient-reported severity and quality of life scores (Patient-Oriented Eczema Measure, Dermatology Life Quality Index), serum vitamin D levels, total IgE serum levels, weeks of satisfactory control, inter-visit cumulate consumption of TAT, and synthetic patient-reported satisfaction at the end of each winter.

All analyses will use procedures available in SAS software 9.4 (SAS Institute, Carry, NC, USA).

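### Randomisation is stratified by clinical site, but the main model adjusts for a north/south region and calls it an allocation variable; the two statements need reconciling

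*Protocol article*

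**What the plan says.** The section on sequence generation and allocation concealment describes permuted blocks of random size. It gives the stratification factors in these words: "with stratification according to the clinical site, age (three age groups) and disease severity (two groups: moderate or severe"). Patients are allocated 1:1 to vitamin D or placebo and "within each arm to either the sequence UV–observation or the sequence observation–UV", which gives four cells.

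Under statistical methods, after the terms of the two primary models are listed, the article says: "Adjustment will be made on the variables used in the allocation process (region – north vs. south"). The remaining covariates in that list are given as "age as a continuous variable, and disease severity (moderate vs. severe"). No site or centre term appears in either model. The same section adds: "The main analysis will be based on the adjusted model". The covariate list therefore belongs to the main analysis of both PO-SCORAD and winter TAT consumption.

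Two other places bear on the geography. Study setting says: "The study will be conducted in 16 French hospital centers". Recruitment says: "Each region is organized from a university-based dermatology department into several ‘field study sites". There, a region is a catchment organised from one university department, not half of the country. Nowhere does the article say that region was an allocation factor, that sites are pooled for the analysis, or which centres count as north and which as south.

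**The concern.** Age and severity carry over from the allocation text to the model. Site does not: a two-level region takes its place under the label of an allocation variable. The two statements cannot both be right as written unless an unstated pooling step lies between them.

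Two things are at stake. First, an analysis should account for the factors that constrained the randomisation. If site predicts outcome and is left out, its variance stays in the error term of between-patient comparisons. Vitamin D versus placebo is such a comparison, and the Background calls it the main trial. Second, while the text is unresolved, the geographic covariate of the main analysis (site, or an undefined north/south split) could be settled after the data are seen.

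**Working it through.** **1. The plan's own figure.** The sample size section gives 340 for a parallel design, halves it for the crossover, and allows 10–15% dropout. 340/2 = 170, and 170/(1 − 0.15) = 200, which matches the stated enrolment. Nothing below changes this number.

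**2. How different the two randomisations are.** The article gives three age groups, two severity groups and 16 centres. That a site is a hospital centre is an assumption. The recruitment text mentions several field study sites per region, so the number of sites could be larger.
- Stratified by site: 16 × 3 × 2 = 96 strata; 200/96 = 2.1 patients each.
- Stratified by region: 2 × 3 × 2 = 12 strata; 200/12 = 16.7 patients each.

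**3. Effect on the vitamin D comparison.** The article gives no between-site intraclass correlation (ICC), so a range was assumed. The simulation used 3,000 runs per setting, 200 patients spread at random over 16 sites (eight per half of the country), and permuted blocks of 4 within site × age × severity. The block size is assumed, since the article says only that sizes are random. The SD of a patient's one-year average PO-SCORAD was set at 14.3. This follows from the article's SD of 18, base correlation 0.6, decay 0.05 and 10–12 measures, which give 14.27 to 14.35. Of the variance not due to site, 70% was assumed stable between years and 30% year-specific. The outcome was the two-year patient mean. Site was fitted as fixed effects.

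| Assumed ICC | Mean SE, region in model | Mean SE, site in model | Ratio | Type I error, region | Type I error, site |
|---|---|---|---|---|---|
| 0 | 1.869 | 1.900 | 0.98 | 0.045 | 0.048 |
| 0.05 | 1.868 | 1.850 | 1.01 | 0.051 | 0.049 |
| 0.10 | 1.876 | 1.806 | 1.04 | 0.048 | 0.055 |
| 0.20 | 1.873 | 1.701 | 1.10 | 0.036 | 0.047 |

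The Monte Carlo error of the rejection rates is √(0.05 × 0.95/3000) = 0.004.

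Hand check at ICC 0: the variance of the two-year mean is 14.3² × (0.7 + 0.3/2) = 204.49 × 0.85 = 173.8. With 100 patients per arm, SE = √(173.8 × 4/200) = 1.86, against 1.869 simulated.

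**4. Effect on the phototherapy comparison.** Each patient contributes a year with and a year without phototherapy at the same site, so an additive site effect drops out of the difference. The simulated type I error of this contrast was 0.041 to 0.056 across the four ICC settings.

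**The case against.** The strongest defence is that the analysis text simply gives the coding of the allocation factors in the model: age becomes continuous, severity stays binary, and site is pooled to north/south. Pooling many small centres is an accepted choice, and the change of age coding is unobjectionable. This reading is possible, but the article does not state it, and its other use of the word region does not support it. Even on this reading, the pooling needs to be stated and the halves defined.

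A second objection is that the stated sample size was built for the phototherapy main effect, which site barely touches. This stands.

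A third is that strata of about 2 patients leave most blocks incomplete, so stratification by site balances only partly and there is less conservatism to correct. This also stands, and it fits the near-nominal type I error at ICC 0.05 and 0.10. The loss of precision from omitting a predictive site effect remains, because it does not depend on how well the blocks balanced.

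A reader might go further and infer that the primary analysis is invalid, that type I error is inflated, or that vitamin D loses a definite amount of power. The documents support none of these. The simulation shows no inflation with the region-adjusted model, and the article states no vitamin D effect size or site variance from which to compute a power loss. A particular effect on TAT consumption through local prescribing habits is likewise conjecture, since the article reports no such differences.

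**Conclusion.** The concern holds as an internal contradiction about the geographic factor, in a model that the article makes its main analysis. The contradiction itself rests on no assumption. Its size does. For the between-patient vitamin D contrast, omitting site is near neutral at an ICC of 0 to 0.05, and widens the standard error by about 4% at 0.10 and about 10% at 0.20. In that last setting the region-adjusted test is conservative (0.036 against 0.05). These figures depend on the assumed ICC, 16 sites, blocks of 4, and the PO-SCORAD variance structure; TAT consumption was not simulated. The phototherapy contrast is largely unaffected as long as site effects are additive. The point is worth correcting because it is cheap and closes an open choice in the main model, not because it threatens the trial's validity.

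**What to change.** Confirm from the web randomisation system which geographic factor was used, and make the allocation section and the statistical methods section name the same one.

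- If it was site: add clinical site as a random intercept to both primary models, keeping age and severity. Region may stay as a covariate, for example as a proxy for sun exposure. A random intercept allows this, whereas fixed effects for every site would absorb region. It also avoids spending 15 degrees of freedom on 16 sites; the fixed-effects version cost about 2% in standard error when site had no effect. If pooling to north/south is preferred, justify it before the data are analysed and list the centres in each half.
- If it was region: correct the allocation text, and the model can stand.

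The cost is one corrected sentence and at most one model term. Site is needed for stratification if it was the factor used, so no new data are required, and enrolment stays at 200. The article describes the trial as still recruiting, so the correction could precede the analysis.

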### Sample size

We used the General Linear Multivariate Model Power & Sample Size (GLIMMPSE) software [30] to calculate the sample size for a repeat measure analysis with a desired power of at least 80%, a Type I error set at 0.05, and equal group sizes. The main predictor variable is phototherapy (yes or no) and the response variable is numerical (PO-SCORAD). Repeat measures are described as follows: 10 to 12 measures with time as the unit, and an equal distance between repeat numerical measures (every 4 weeks); we entered means for each time according to an anticipated evolution over time, and standard deviations of the response variable were set at 18. GLIMMPSE currently assumes that the standard deviation is constant across repeat measures. As we have some uncertainty about what standard deviation value to use, we used alternative values for variability and computed power for half the variance, the variance as specified, and twice the variance; this was also applied to means. GLIMMPSE automatically combines the sources of correlation into a final covariance matrix using a structured correlation based on the linear exponential auto-regressive model. The model describes a correlation that decreases monotonously with the distance between measures; the base correlation is set at 0.6 and the decay rate at 0.05. It can be noted that the minimum clinically significant difference for the PO-SCORAD score is indeed around 9, but we adopted a stance enabling the detection of a smaller difference, which means we are in an even better position to detect a clinically relevant difference.

We considered a main effect hypothesis test for the effect of a single predictor variable averaged across all other factors. We used the Hotelling–Lawley trace as the recommended statistical test for this kind of design, with a simple ‘between’ hypothesis and a complex ‘within’ hypothesis. We indeed plan to use a mixed model for our data analysis, and we will use the Wald test with Kenward–Roger degrees of freedom. It can be noted that the Hotelling–Lawley trace test for the general linear multivariate model coincides with the Wald test for the general linear mixed model.

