### Participant timeline

Following the opening of screening in January, patients can enter the study at any time; they will go through a pre-screening period until they are randomized in September. We have chosen a common fixed period for inclusion to avoid confounding seasonality factors. During the pre-screening period, trial outcomes are collected but no treatment is given. Enrollment is preceded by a pre-screening period of 9 months to identify patients with inclusion criteria, and exclude, before randomization, any participants who are unlikely to be adherent. A patient will be in the trial for 2 years post-randomization (i.e., until September 2019 for those entering in September 2017). After the inclusion visit, visits will occur every 3 months over 2 years. Furthermore, each patient will complete the self-administered questionnaires including the PO-SCORAD at home through an application on their computer or phone, or otherwise on paper, every 4 weeks. The time schedule of enrolment and visits is provided in Table 1 and Fig. 1.

**Table 1 Tab1:** Time schedule of enrolment and visits

Actions	Visit 0 Screening	Visit 1 Inclusion	Visits 2–8 Follow-up	Visit 9 End of trial
Written informed consent	X			
Web-based randomization		X		
Demographic details	X	X		
Medical history	X	X	X	X
Physical examination	X	X	X	X
Investigator Global Assessment	X	X	X	X
Eczema Area and Severity Index, Severity of Atopic Dermatitis Index		X	X	X
Quality of Life: Dermatology Life Quality Index		X	X	X
Patient-Oriented Severity of Atopic Dermatitis Index, Patient-Oriented Eczema Measure	X	X	Computer record every 4 weeks	X
Estimation of solar exposure		X	X	X
Complete blood count, serum chemistry, serum creatinine, serum calcium and phosphate, serum parathyroid level	X			X
Serum total IgE level		X	X	X
Vitamin D dosage		X	X	X
Delivery of oral vitamin D or placebo vial		X	X	
Checking for adverse events			X	X

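### The primary PO-SCORAD model adjusts for baseline severity only as moderate versus severe and leaves out the inclusion PO-SCORAD, which costs precision in the vitamin D comparison

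*Protocol article*

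**What the plan says.** All references are to the protocol article.

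- **Model.** Statistical methods lists the terms of the model for the first primary outcome (E1, repeated PO-SCORAD): phototherapy, vitamin D, period, order, carry-over and interactions. It then adds the adjustment variables: region (north or south), "age as a continuous variable, and disease severity (moderate vs. severe"). The same section makes this adjusted model the main analysis. Baseline PO-SCORAD is named neither as a covariate nor as part of the response.
- **Data at hand.** Table 1 marks PO-SCORAD at screening (Visit 0) and at inclusion (Visit 1). Participant timeline adds: "During the pre-screening period, trial outcomes are collected but no treatment is given".
- **Sample size.** It was worked out for phototherapy: "The main predictor variable is phototherapy (yes or no"). The inputs are "a desired power of at least 80%, a Type I error set at 0.05, and equal group sizes"; "standard deviations of the response variable were set at 18"; "10 to 12 measures with time as the unit"; and "the base correlation is set at 0.6 and the decay rate at 0.05". The parallel-arm total of 340 was halved because of the crossover, and 200 are to be enrolled.
- **Vitamin D.** Trial design makes it a parallel-group comparison, and the Background labels it the main trial. No separate sample size is given for it.

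**The concern.** In the phototherapy crossover each patient is their own control, so stable differences between patients cancel. In the vitamin D comparison they do not: they enter its standard error in full, apart from what the covariates explain. A baseline value of the same score is usually the best single predictor of such differences. The plan replaces it with a two-level category, which keeps only part of the information and corrects chance baseline imbalance in the outcome only coarsely.

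This matters most for vitamin D because the halving of the sample size does not help it. By the protocol's own inputs a parallel comparison needs 340 patients, and vitamin D gets 170 to 200.

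**Working it through.** **1. The plan's own figure.** 340 / 2 = 170, and 170 / (1 − 0.15) = 200, as stated.

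**2. The implied difference.** The means behind the 340 are in an additional file that is not shown, so the difference is back-solved. The alpha is the "same two-sided level of 0.05". The SD of a patient's mean of 12 measures is 18 × √(mean of the correlation matrix). The decay of 0.05 can be read in two ways:

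- spread over the whole follow-up range: 18 × √0.629 = 14.27
- applied per 4-week step: 18 × √0.590 = 13.82

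With 170 per arm, difference = (1.96 + 0.84) × SD × √(2/170). This gives about 4.35 and 4.2 points (t distribution). Taking 10 measures instead of 12 moves these by less than 0.1.

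**3. The vitamin D comparison.** Take the patient mean over 24 measures (two years) and 85 patients per arm. Let v be the variance of that mean in units of 18², c the average correlation of the baseline score with the follow-up scores, and f the share of baseline variance that the moderate/severe category captures. The category is assumed to predict follow-up only through the baseline score. Then

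- planned model: residual SD = 18 × √(v − f·c²)
- continuous baseline: residual SD = 18 × √(v − c²)

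The documents do not give f. A range of 0.25 to 0.64 is assumed; 0.64 (2/π) is a median split of the same normally distributed score. The value of c is obtained by extending the protocol's correlation structure back to baseline. Power is evaluated at SE = SD × √(2/85) = 0.153 × SD.

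| Reading of the decay | v | c | Difference | SD, planned model | SD, continuous baseline | Power, planned model | Power, continuous baseline |
|---|---|---|---|---|---|---|---|
| Whole range | 0.612 | 0.592 | 4.35 | 13.0 to 11.2 | 9.2 | 58% to 71% | 87% |
| Per step | 0.523 | 0.454 | 4.2 | 12.4 to 11.3 | 10.1 | 60% to 68% | 77% |

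Example, first row: 18 × √(0.612 − 0.351) = 9.2; SE = 0.153 × 9.2 = 1.41; 4.35 / 1.41 = 3.08; 3.08 − 1.96 = 1.12, which is a power of about 87%.

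The gain is 16 to 29 points on the first reading and 9 to 17 on the second. On the first reading, the difference detectable with 80% power falls from about 4.8-5.6 to 4.0 points.

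**4. A weaker baseline correlation.** Keep v = 0.612 and a difference of 4.35:

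- c = 0.3: power goes from 53-56% (planned) to 58%, a gain of about 2 to 5 points.
- c = 0.4: power goes from 54-59% to 64%, a gain of about 5 to 10 points.

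The per-step reading (v = 0.523, difference 4.2) gives about 3 to 12 points over the same range of c.

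**5. A larger effect.** At 9 points and with no baseline information at all, SD = 18 × √0.612 = 14.1, SE = 2.16, and 9 / 2.16 = 4.17. Power is about 98-99%.

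**6. Simulation check** (2000 replicates, 170 patients). The SE of the vitamin D effect is 1.71 to 1.92 with a two-level severity term and 1.42 with the continuous baseline. The SE of the phototherapy contrast is 0.41 to 0.42 whichever covariate is used.

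**The case against.** The strongest case against the point is as follows.

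- **The planned model is not unadjusted.** A reader might compare about 52% power, which is what a model with no severity term gives, with the 87% above. The plan does include severity, so its own starting point is 58-71%. This objection stands, and the gains above are measured from the planned model.
- **The correlation of 0.6 is borrowed.** The protocol states it for follow-up scores 4 weeks apart within a year, not for baseline against follow-up or across two years. Baseline falls in September, in patients selected for improving in summer, and entry requires an Investigator Global Assessment above 2, which narrows the baseline range. Both features argue for a lower value. This stands too, and it is why the gain has to be given as a range that reaches down to about 2 points.
- **No vitamin D effect is assumed in the text.** The 4.2 to 4.35 points are back-solved from the phototherapy calculation. A reader might infer that the trial cannot detect a clinically relevant vitamin D effect. The documents do not support that: at the 9 points they cite as the minimum clinically significant difference, power is already about 98%. The shortfall is relative to the 340 patients and to the protocol's declared aim of detecting less than 9 points.
- **Nothing is biased.** Adjusting for the allocation variables is a legitimate pre-specified choice, and randomisation protects the comparison. This stands in full.
- **An analysis plan not shown could add the covariate.** That is possible, but the article itself lists the adjustment set and makes that model the main analysis. As written, the choice is made rather than deferred.

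**Conclusion.** The point holds as a loss of efficiency in one comparison. The E1 model leaves out a pre-treatment value of its own outcome that is already scheduled, and vitamin D versus placebo pays for it.

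Under the protocol's SD and correlation, the back-solved difference and f between 0.25 and 0.64, vitamin D power at 170 patients would rise from about 58-71% to about 77-87%. If the September score predicts follow-up with a correlation of only 0.3 to 0.4, the gain is about 2 to 10 points (up to 12 on the per-step reading of the decay). The baseline correlation, f and the difference are assumptions; the article gives none of them.

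A reader might also infer that the phototherapy result is weakened. The simulation shows no material change in its standard error for patients with both years.

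The change is worth making because it is nearly free and falls on the comparison labelled the main trial. The trial is not invalid without it.

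**What to change.** - In Statistical methods, add the Visit 1 (September) PO-SCORAD as a continuous covariate in the E1 model, and keep region, age and severity. Randomisation can take place on the day of Visit 1, so state that the score is recorded before allocation is known and before the first vial.
- Do the same for the secondary scores measured at Visit 1, each with its own baseline.
- Do not use the mean of the pre-screening values. Patients enter at any time from January to September, so these values differ between patients in number and season, which the common September inclusion was meant to avoid.
- Write the change in before unblinding, so that it cannot look data-driven.

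The cost is one degree of freedom and one line of analysis text. No new data are needed, because Table 1 already schedules the measurement.

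### POEM is scheduled as a 4-weekly home record, but the secondary analysis rule limits it to four clinic-visit measures a year, leaving about 8 of 12 yearly records unused

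*Protocol article*

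**What the plan says.** **Collection.** In Table 1 (Participant timeline), one row covers "Patient-Oriented Severity of Atopic Dermatitis Index, Patient-Oriented Eczema Measure". Its entries are a cross at Visit 0, a cross at Visit 1, "Computer record every 4 weeks" for Visits 2–8, and a cross at Visit 9. EASI, SCORAD, IGA and DLQI have a plain cross at Visits 2–8; POEM does not. The text of the same section agrees: "each patient will complete the self-administered questionnaires including the PO-SCORAD at home through an application on their computer or phone", or on paper, at 4-week intervals. The plural, and the fact that PO-SCORAD is given as one of them, fit a table row that holds both scores.

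**Visits.** The Participant timeline section says: "After the inclusion visit, visits will occur every 3 months over 2 years". That is four a year. The Recruitment section gives another interval: "scheduled visits will take place every 6 weeks".

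**Analysis.** For PO-SCORAD, Statistical methods counts "up to 12 measures for each 1-year period, on the PO-SCORAD". For the secondary analyses it says "we will use up to four measures per 1-year period, collected at each clinical visit (every 3 months"), and the list that follows includes "patient-reported severity and quality of life scores (Patient-Oriented Eczema Measure, Dermatology Life Quality Index"). The article describes no separate analysis of the 4-weekly POEM series.

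**The concern.** For POEM, the analysis sentence disagrees with the schedule in two ways. It describes collection at clinic visits where Table 1 shows none between Visit 1 and Visit 9, and it uses 4 values a year where the schedule yields about 12. It also does not say which home record stands for a visit, and a 4-weekly record need not fall on a 3-monthly visit. Phototherapy is open-label, so that choice is better fixed before the data are seen.

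At stake is precision on a patient-reported secondary outcome. The Discussion presents serial measurement of signs, symptoms and quality of life as one of the two routes to assessing long-term control. Patients are asked for POEM every 4 weeks, and most of what they supply would not enter the stated analysis.

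**Working it through.** **1. Counting records.**
- Clinic visits: 12 months / 3 = 4 a year. Visits 2–9 are 8 visits over 2 years, which agrees with the stated maximum of four.
- Home records: 48 weeks / 4 = 12 a year, which agrees with the stated maximum of 12 for PO-SCORAD. A full calendar year gives 52 / 4 = 13. The sample size section uses 10 to 12.
- Unused share = (m − 4)/m: 6/10 = 60%, 8/12 = 67%, 9/13 = 69%.
- In a winter of about 26 weeks there would be about 6 home records against about 2 visit measures.

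**2. Inputs for precision.**
- From the Sample size section, stated for PO-SCORAD: linear exponential autoregressive correlation, base 0.6, decay 0.05. *Assumption:* POEM follows the same pattern.
- *Assumption:* a correlation c between measures in different years. The article gives no value, so a range is shown.
- *Simplification:* simple yearly means with no missing home records.

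**3. Variance of one patient's yearly mean**, in units of the single-measure variance. The correlation at a distance of d 4-week steps is 0.6^(1 + 0.05(d − 1)/10), which runs from 0.600 at one step to 0.585 at eleven. V is the average of all entries of the correlation matrix.
- 12 measures: V₁₂ = 0.6287
- 4 measures (every third record): V₄ = 0.6954
- Ratio 0.6954 / 0.6287 = 1.106, so the standard error (SE) is √1.106 = 1.05 times as large.

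**4. Phototherapy contrast (within patient, year against year).** The variance is proportional to 2(V − c), so the SE ratio is √[(V₄ − c)/(V₁₂ − c)].

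| c (assumed) | V₄ − c | V₁₂ − c | Variance ratio | SE increase |
|---|---|---|---|---|
| 0.2 | 0.4954 | 0.4287 | 1.16 | about 8% |
| 0.3 | 0.3954 | 0.3287 | 1.20 | about 10% |
| 0.4 | 0.2954 | 0.2287 | 1.29 | about 14% |
| 0.5 | 0.1954 | 0.1287 | 1.52 | about 23% |
| 0.58 | 0.1154 | 0.0487 | 2.37 | about 54% |

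At c = 0.4 the loss equals having 1 − 1/1.29 = 23% fewer patients for this outcome. If the decay is instead read as applying per 4-week step, the increases at c = 0.2, 0.4 and 0.5 are about 8%, 16% and 32%.

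**5. Vitamin D contrast (between patients).** Averaging over both years, 8 against 24 measures gives an SE ratio of 1.027, about 3%. For a single yearly mean it is 1.05 (step 3).

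**The case against.** The best case on the other side is that the sentence in Statistical methods is a loose umbrella, not an exclusion rule. The same list contains satisfaction at the end of each winter, which arises once a year, and weeks of satisfactory control, which is not a point measure at a visit. A journal article condenses, and the modelling of each secondary outcome is commonly left to an analysis plan that is not shown here. A common 3-monthly grid is also a legitimate and unbiased choice. This lowers the weight of the point but does not remove it: the article states both a schedule and a rule, and for POEM they disagree. Loose drafting would still need correcting.

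Three stronger readings are tempting, and the article does not support them.
- *A reader might infer that two thirds of the information is lost.* Two thirds is the share of records. Repeated scores on one patient are correlated, so the loss of precision is much smaller.
- *A reader might infer that a main outcome is weakened, or that winter flares between visits escape the trial.* POEM is one of several secondary outcomes and lies outside the hierarchical test. PO-SCORAD, with up to 12 measures a year, covers the intervals between visits, and weeks of satisfactory control is a separate outcome.
- *A reader might take an SE increase above 50% as the size of the problem.* That needs a between-year correlation of about 0.58, almost equal to the 0.6 assumed for adjacent 4-week records. It cannot be ruled out, but it is the extreme of an assumed range.

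**Conclusion.** The point holds as a conflict between the POEM schedule in Table 1 and the POEM analysis rule in Statistical methods. As written, about 8 of 12 yearly records (range 60% to 69%) go unused. If the PO-SCORAD planning correlation applies to POEM and the between-year correlation lies between 0.2 and 0.5, the SE of the phototherapy contrast is about 8% to 23% larger than it need be, and more if that correlation is near 0.6. The vitamin D contrast loses about 3% to 5%. Neither correlation is given for POEM, so these figures are a sensitivity range and not a demonstrated loss. The primary outcomes, their ordered testing and the sample size are unaffected. The point merits correction before analysis because using all the records gains precision at no real cost.

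**What to change.** Take POEM out of the four-measure list in Statistical methods, and state that all scheduled 4-weekly POEM records will be analysed with the same repeated-measures mixed model as PO-SCORAD. Keep the 3-monthly rule for the outcomes measured at visits: EASI, SCORAD, IGA, DLQI and the serum measures. If POEM is in fact taken only at visits, correct Table 1 instead.

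The 6-week visit interval in the Recruitment section and the 3-month interval in Participant timeline should be reconciled at the same time, since the limit of four measures rests on the latter.

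The cost is wording only. No data collection beyond the existing schedule is needed.
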